DREAMS investments aim to ensure that AGYW in selected DREAMS areas (sub-national units with high HIV burden) have access to all core package interventions, either through DREAMS funding or additional PEFPAR funding schemes (e.g., for VMMC) or coordination with national government programmes (e.g., for cash transfers or educational subsidies). PrEP is planned for selected countries and sites within countries, as determined by national governments. Guidance for each component of the core package has been provided to countries by PEPFAR, and coverage targets have been set for each sub-national unit by age group, area and intervention [9]. ‘Primary’ interventions are the priority interventions from the core package that all AGYW in an age group should receive. ‘Secondary’ interventions are needs-based interventions from the core package, recommended for specific sub-populations of AGYW based on additional circumstances, e.g., condom provision for AGYW who are sexually active; post-violence care for those who have experienced sexual violence. Additional file 1: Table S1 summarises the primary and secondary interventions in each country setting.

The way in which the various DREAMS components are rolled out and coordinated, and the timing of implementation will differ in each evaluation site, depending upon: the capacity and readiness of Implementing Partners (IPs) contracted by the United States Government to implement DREAMS services; the timing of contractual arrangements with IPs; negotiations with national governments; finalization of sex education curricula for schools; and other contextual factors. Given the heterogeneity in DREAMS’ delivery, we will monitor how, when, by whom, and to whom, components of the DREAMS package are delivered, in the process evaluation activities described below [10].

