^a^not collected in Nairobi

^b^know they are HIV+ or have tested HIV negative in the past 12 months

^c^ do not want a child in next 2 years or ever but not using a method to prevent pregnancy

^d^ uMkhanyakude only

^e^ Used condom at last sex (in past 12 months); Any condomless sex in last 1 month / last 12 months and in the last 3 months

For component 2, the nested cohorts of AGYW designed to measure pathways of change, the primary exposure is uptake of DREAMS interventions among individual AGYW, considering single components as well as the number and combination of components of the core package that were received. The extent to which AGYW are aware of, invited into, and participate in DREAMS interventions will be summarized, using the core package and primary/secondary interventions as frameworks to categorise interventions and standardize across the settings. (See Table 3 for proposed, a priori measures of DREAMS uptake.) Comparisons of mediators and secondary outcomes will then be made among AGYW according to their uptake of DREAMS interventions.

**Table 3 Tab3:** Outcomes, mediators of change in the outcomes, and uptake of DREAMS interventions, to be captured via nested DREAMS cohorts of adolescent girls and young women (in Kenya and South Africa) and young women who sell sex (in Zimbabwe)

	AGYW (South Africa and Kenya)		YWSS (Zimbabwe)
	13–17 years^b^	18–22 years^b^	18–24 years
Primary	n/a ^a^		HIV incidence
Secondary Outcomes	Knows HIV status		
	Number of lifetime pregnancies		
	Reduced experience of violence		
	Incidence & prevalence of HSV-2/other STI		HIV prevalence
	Aware of partners’ HIV status		Number of sexual partners
			Engaged in transactional sex for economic reasons
	Age at first sex	Number of sexual partners in the last 12 months	Use of condoms & PrEP with regular/transactional sex partners
	Age at first /subsequent pregnancies	Age at first / subsequent pregnancies	Adherence to HIV treatment and care services
	Condom use		Reduced food insecurity
	Unmet need for contraception		
	Age-disparity with sexual partners	HIV risk of sexual partners (to be defined a priori)	
	No/less transactional sex		
	Stay in school	In employment or completed vocational / microfinance training	
	Age at first marriage or first long-term/live-in partner		

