Mediators of change (Sample measures of constructs that DREAMS aims to improve, specifically: social assets, personal safety, self-efficacy, common mental disorders, empowerment, gender equitable norms, and sexual relationship power)	Have at least one trusted female friend they can confide in		Have at least one trusted female friend they can confide in
	Meet regularly in a safe place with peers		Meet regularly at community mobilization sessions with peers and has increased sense of social cohesion
	Know a woman, other than mother/guardian, to turn to if have a serious problem		Can access HIV prevention services including condoms, STI treatment & PrEP (as measure of self-efficacy) and contraceptives
			Is supported to adhere to PrEP, and economically able to adhere/access PrEP
	Able to avoid / refuse sex if sex is not wanted		Has comprehensive knowledge of HIV prevention
	Able to refuse sex if partner will not use a condom (or confident they can use a condom with all sex partners)		Have access to money in an emergency
	Confident they could get a HIV test		Is confident she can negotiate condom use with sexual partners (including clients)
	Confident they can access health services when they need them (sexual and reproductive health services in particular)		Able to avoid violent relationships
	Have access to their own savings		
	Have access to money in an emergency		
	Believes a man and woman should decide together whether to use a condom / what type of contraception to use		
Uptake of DREAMS interventions	• Invited to participate / enrolled in DREAMS • Received at least one DREAMS intervention • Received multiple intervention categories in the DREAMS core package • Received DREAMS primary or secondary interventions (depending on age and need)		Intervention sites (versus comparison sites)
			Within intervention sites, measures of individual uptake will include: • Received at least one DREAMS intervention • Received DREAMS package for key populations (‘KP_Prev’^c^) • Received KP_Prev + educational subsidies or vocational training • Received KP_Prev + PrEP

^a^In South Africa and Gem, Kenya, HIV incidence will be estimated from the larger population-level studies (see Table 2), for adequate statistical power (see ‘Sample Sizes’ below)

^b^ Age at enrolment, to be followed over two years

^c^‘KP_Prev’ is the PEPFAR indicator used to measure DREAMS package for key populations and includes condom promotion, HIV testing services, and social asset building [22]

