These analyses will adjust for important confounding variables measured at enrolment (for example, household socio-economic position) and an AGYW’s “propensity to receive” DREAMS interventions. This is because the criteria used by DREAMS implementing partners to select AGYW who will be invited to participate in the programme are also likely to influence the outcomes that are to be measured, i.e., they may be risk factors for HIV incidence and the secondary outcomes, and so may confound observed associations between uptake of interventions and these outcomes. For example, Implementing Partners are prioritising girls considered to have the highest risk of HIV infection (such as, those who are living in relatively poor households, are orphans, are out of school, or are young mothers, as identified via the ‘Girl Roster’ enumeration exercise and by community-based organisations) [19]. The characteristics that predict exposure to DREAMS will be identified using HDSS data, and the information across these characteristics will be synthesized into a single “propensity to be exposed to DREAMS” score (equivalent to an estimated probability of exposure to DREAMS, and taking values between 0 and 1), and AGYW will be categorized (stratified) into 4–5 groups on the basis of their propensity score. The association between uptake of DREAMs interventions and socio-economic and behavioural outcomes will be adjusted for the propensity score (in categories) as well as the individual characteristics that are the most important confounding variables.

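### In the nested cohorts, uptake counts include needs-based components triggered by violence or sexual activity, so for those outcomes the dose is confounded by need that arises during follow-up

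*Protocol article*

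**What the plan says.** Under Measurement and analysis of key variables, the main exposure for component 2 (the nested cohorts) is each girl's uptake, "considering single components as well as the number and combination of components of the core package that were received". The same section adds: "Comparisons of mediators and secondary outcomes will then be made among AGYW according to their uptake of DREAMS interventions". One of the uptake measures that Table 3 proposes for Kenya and South Africa is "Received multiple intervention categories in the DREAMS core package"; it does not separate primary from secondary components. Another is "Received DREAMS primary or secondary interventions (depending on age and need").

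The section on the core package explains that secondary "interventions are needs-based interventions from the core package, recommended for specific sub-populations of AGYW based on additional circumstances". Its examples are "condom provision for AGYW who are sexually active; post-violence care for those who have experienced sexual violence". Table 3 lists "Reduced experience of violence" as a cohort outcome, together with age at first sex, number of pregnancies and condom use.

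Analysis of causal pathways assesses outcomes at 12 and 24 months. It adjusts for confounders measured at enrolment, for a propensity score in 4–5 groups, and for the most important individual confounders. The score is described as "equivalent to an estimated probability of exposure to DREAMS, and taking values between 0 and 1". The article does not list the individual confounders, and it does not require counted uptake to come before the outcome window.

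**The concern.** Taken together, these statements let the outcome cause the exposure. A girl who experiences sexual violence during follow-up may receive post-violence care because of it. Her count rises by one, and she also has the outcome. A girl who starts having sex may be given condoms for that reason. In both cases a higher count goes with the outcome even if the programme changes nothing.

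The planned adjustment addresses a different problem, namely selection into the programme. Its examples (poor households, orphans, girls out of school, young mothers) are reasons for being invited. A score for the probability of exposure does not, by its construction, balance need between girls with one component and girls with three. Covariates fixed at enrolment carry no information on need that arises afterwards.

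What is at stake is one of the evaluation's three questions, the pathways of effect. The mediation step splits up the uptake effect, so it would inherit any bias in that effect.

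**Working it through.** The article gives no effect size, uptake rate or trigger rate for this analysis, so there is no figure of its own to reproduce. The check is a simulation with no programme effect.

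**Inputs from the article.** Cohort size is 2 × 400 = 800 (minimum per age group, Sample sizes). Adjustment is by five propensity strata plus individual enrolment covariates (Analysis of causal pathways).

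**Assumptions, not in the article.** The risk of violence is about 20% at average covariates. About half of girls have any uptake. There are four primary components, each received with probability 0.6 once in the programme. One needs-based component is triggered by violence before enrolment with probability *tb*, or during follow-up with probability *tf*. Prior violence is a covariate unless stated. There were 500 replicates, with a logistic model and a two-sided 5% test.

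**Results for violence during follow-up, need arising in follow-up only (tb = 0).** Odds ratio, with false-positive rate in brackets:

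| *tf* | per extra component, recipients | 3+ versus 1–2 components |
|---|---|---|
| 0.1 | 1.13 (15%) | 1.17 (9%) |
| 0.3 | 1.38 (75%) | 1.51 (42%) |
| 0.6 | 1.87 (100%) | 2.42 (96%) |

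**Check by hand of the last column.** With Binomial(4, 0.6) primary components, the probabilities of 0, 1, 2, 3 and 4 are 0.0256, 0.1536, 0.3456, 0.3456 and 0.1296.
- Without violence, the odds of 3+ versus 1–2 are (0.3456 + 0.1296)/(0.1536 + 0.3456) = 0.4752/0.4992 = 0.952.
- With violence, the extra component moves a share *tf* of those with two primary components up to three, and of those with none up to one. The odds become (0.4752 + 0.3456 *tf*)/(0.4992 − 0.3456 *tf* + 0.0256 *tf*).
- *tf* = 0.1: 0.50976/0.4672 = 1.091; ratio 1.091/0.952 = 1.15.
- *tf* = 0.3: 0.57888/0.4032 = 1.436; ratio 1.51.
- *tf* = 0.6: 0.68256/0.3072 = 2.222; ratio 2.33.

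These agree closely with the simulation. No enrolment covariate appears in the formula. The ratio is the same in every stratum, which is why enrolment adjustment cannot remove it.

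**Other scenarios.**
- Need before enrolment only (*tb* = 0.5, *tf* = 0): 1.07 per component (10%) with the score alone, and 1.00 (6%) once prior violence is a covariate.
- Both sources (*tb* = 0.5, *tf* = 0.3): 1.27 per component (53%).
- Any receipt versus none: 0.99 to 1.05 (5–6%).
- Primary components only, 3+ versus fewer among recipients: 0.97 to 1.02 (4–7%) in every scenario.
- In a companion run at *tf* = 0.3, the count per component gave 1.08 (24%). That is the size to expect when non-recipients stay in the model at zero, because most of the variation in count is then entry into the programme.

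**Condom provision triggered by sexual activity.** This was a second null run with 400 replicates. Provision reached half of sexually active participants in the programme. Sexual activity at enrolment was not a covariate, so these figures mix need before and after enrolment. Odds ratios per component were: ever had sex (standing in for sexual debut) 1.12 (64%); pregnancy 1.05 (13%); condom use among all girls 1.06 (20%); condom use among the sexually active 1.00 (4%).

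**The case against.** The strongest reply is that the plan does more than apply a propensity score. It also adjusts for individual confounders at enrolment and openly discusses risk-based selection. It uses the primary/secondary split to categorise interventions, and one Table 3 measure refers to age and need. The covariate list, and the dating of uptake, could well be in an analysis plan that is not shown. The trigger rates above are assumed. Table 3's violence outcome is not limited to sexual violence, so the share of it that triggers post-violence care may be small.

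Much of this stands. Need present at enrolment can be handled if prior violence and sexual activity are covariates. The size of the bias is unknown. The reply does not meet the main point, though. The article itself states the count and combination exposure, draws no analysis rule from the reference to need, and measures its confounders before the follow-up need arises.

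A reader might go further and infer that receiving more components will look harmful in general. The article does not support that:
- Direction depends on the outcome. Condom use among all girls looks slightly better with more components, and among the sexually active it is unbiased.
- Crude comparisons with no adjustment can give odds ratios for violence of roughly 1.5 to 4.4, but they leave out the planned adjustment and should not be attributed to this plan.
- The layering analysis under Study design is at small-area level, with dose as a percentage of girls. The simulation does not address it.
- Stratifying the score into 4–5 groups rather than weighting is a matter of preference, not an error.

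**Conclusion.** The concern holds for a defined set of analyses: count or combination uptake in the nested cohorts, for outcomes that overlap with a trigger. These are experience of violence and sexual debut and, to a lesser degree, pregnancy. For violence, with the planned adjustment and no true effect, the odds ratio per extra component among recipients is about 1.1 to 1.9 for follow-up trigger probabilities of 0.1 to 0.6. It is smaller if non-recipients are included as zero. With primary components only, it is about 1.0. These sizes rest on assumed uptake and trigger rates. The mechanism rests only on the article's own definitions. Any receipt versus none is little affected. HIV incidence is compared by calendar period, or between sites in Zimbabwe, and is not affected.

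**What to change.** For outcomes that overlap with a trigger:
- define the main dose as the number, or share, of age-assigned primary components received;
- leave out of the exposure any component whose trigger is the outcome analysed, such as post-violence care when the outcome is violence;
- count only uptake that precedes the outcome window;
- name prior violence and sexual activity at enrolment as covariates;
- fit the propensity model to the dose contrast being analysed, not to exposure in general.

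Needs-based components can be analysed separately among girls whose need was recorded before receipt.

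The cost is some wording and recoding, provided the cohort data date both uptake and need. The main dose will say less about needs-based services; the separate analysis recovers part of that in a smaller group.

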### The DREAMS core package

The DREAMS Partnership supports a core package of interventions targeted at AGYW, their families, wider communities, and men characterized to be the sexual partners of AGYW [7]. The package is comprised of evidence-based interventions shown to address HIV risk behaviours, HIV transmission, socio-economic vulnerabilities and gender-based violence (Table 1).

**Table 1 Tab1:** Interventions and target populations of the DREAMS Core Package

Target population and strategy	Evidence-based intervention
*Individual interventions (delivered directly to adolescent girls and young women)*	
Empower girls and young women and reduce their risk	▪ Condom promotion and provision ▪ HIV testing and counselling services (HTS) ▪ Oral pre-exposure prophylaxis (PrEP) for HIV, offered to a subset of females at exceptionally high risk and in select countries ▪ Post-violence care ▪ Expanded contraceptive method mix ▪ Social asset building
*Contextual interventions (not all delivered directly to adolescent girls and young women but from which they can benefit)*	
Mobilize and strengthen the community for change	▪ School-based HIV and violence prevention for boys and girls ▪ Community-based HIV and violence prevention for boys/young men and girls/young women ▪ Community mobilization and norms change for community leaders, boys and men
Strengthen families	▪ Parenting and caregiver programmes for vulnerable adolescent girls ▪ Social protection (cash transfers, educational subsidy, combination socioeconomic approaches)
Decrease risk in sexual partners of AGYW	▪ Characterisation of male partners to target highly effective interventions, e.g., HIV testing services, antiretroviral therapy (ART) and voluntary medical male circumcision (VMMC)

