#### Zimbabwe

The Zimbabwe evaluation will capitalise on a national programme that provides HIV prevention and sexual and reproductive health services to female sex workers (FSW) in Zimbabwe, known as “Sisters with a Voice”. ‘Sisters’ began in 2009 and provides free access to HIV testing, STI treatment, family planning, HIV prevention education, condoms and legal services to over 65,000 women across 36 sites [16]. Around 40% of FSW accessing the programme are younger than 25 years. The evaluation will include six districts in which the Sisters programme is active: two in which DREAMS+PrEP are delivered (Bulawayo and Mutare) and four comparison sites in which no DREAMS interventions are planned (Karoi, Chinhoyi, Zvishavane and Kwekwe). Comparison sites were selected for their comparability to intervention sites in terms of population size, urban location, and presence of a Sisters with a Voice site with relatively high client volume [8].

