The process evaluation will include five methodologies:Qualitative longitudinal study of young people’s experiences. Young people’s experience of and “journeys” through DREAMS, including barriers and facilitators to what works in practice will be tracked in detail for a small cohort of 20 AGYW and, in HDSS sites only, 20 young men in each site. These cohorts – of DREAMS beneficiaries sampled purposively from the general population (for males) and AGYW cohorts (for females) – will be followed longitudinally and offered a range of ways to share their experiences in real-time including use of diaries and informal interviews.Small group discussions. The experiences of AGYW’s families, parents, partners, and broader communities will be explored through focus and family group discussions. Group discussions in each evaluation setting will help investigate understanding and experience of DREAMS and its components and whether social norms and attitudes are influenced by the interventions.Rapid participatory community mapping. This method will be used in the DREAMS areas to quickly gain a broad understanding of the social context for adolescents and young people and the reach and coverage of the AGYW services at baseline and after two years of DREAMS intervention. The mapping will use rapid appraisal methods with participant observation and short interviews.Interviews with key informants in delivery organizations. Up to 20 individuals responsible for implementing DREAMS activities in each setting will be interviewed to explore views and experiences of, and barriers and facilitators to, DREAMS activities each year. Local health care workers and community and youth leaders will also be interviewed.Observations of DREAMS interventions delivered in context. Using checklists, structured observations will record the ways in which DREAMS is delivered and received, and with what quality and intensity (using DREAMS standard operating procedures for reference). Observations will be made of DREAMS interventions in a range of settings such as schools, safe spaces, and health facilities.

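### Some mediators in Table 3, mainly in the Zimbabwe column, overlap with the DREAMS components that define the exposure, so pathway estimates through those items mix receipt with mechanism

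*Protocol article*

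**What the plan says.** The Theory of change section describes mediators as psycho-social factors, giving empowerment and self-efficacy as examples, that connect uptake to the three pathways of protection. Under Measurement and analysis of key variables, the exposure in the nested cohorts is individual uptake of DREAMS components, singly and in combination.

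Table 3 then lists these items as mediators:

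- Zimbabwe: an attendance part, "Meet regularly at community mobilization sessions with peers", within the full item "Meet regularly at community mobilization sessions with peers and has increased sense of social cohesion".
- Zimbabwe: "Is supported to adhere to PrEP, and economically able to adhere/access PrEP".
- Zimbabwe: "Can access HIV prevention services including condoms, STI treatment & PrEP (as measure of self-efficacy) and contraceptives".
- AGYW in Kenya and South Africa: "Meet regularly in a safe place with peers".

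The uptake block of the same table has, for Zimbabwe, a level that adds PrEP to the key-population package (KP_Prev). PrEP use with partners is a Zimbabwe secondary outcome. Table 1 lists PrEP and social asset building as core components, along with "Community mobilization and norms change for community leaders, boys and men". The process evaluation methods state: "Observations will be made of DREAMS interventions in a range of settings such as schools, safe spaces, and health facilities".

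Under Analysis of causal pathways, step 1 relates uptake to improvement in the mediators. Step 4 estimates how far the effect on secondary outcomes runs through them.

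**The concern.** A mediation analysis needs a mediator that is distinct from the exposure. If one act, such as attending a DREAMS group or being supported on PrEP, scores on both, step 1 finds an association that says nothing about psycho-social change. Step 4 then credits to the mediator an effect that may come directly from receiving the component. At stake, for the items concerned, is the evaluation's second main question: through which pathways DREAMS works.

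**Working it through.** **Document figure.** The article gives no mediated share or expected mediator prevalence, so there is nothing to reproduce. The check compares item wording with the exposure definitions, then illustrates the size.

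**Items against exposure.**

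- *Mobilisation sessions (Zimbabwe).* The item has two parts. Attendance is receipt of an activity; social cohesion is a state. A woman with strong cohesion who does not attend cannot score, so the state cannot be isolated.
- *PrEP support and access (Zimbabwe).* PrEP appears as an uptake level, in two mediator items and as an outcome. Where the exposure is KP_Prev plus PrEP, being supported on PrEP or able to access it is close to the exposure itself.
- *Other parts of the access item (Zimbabwe).* Condoms, STI treatment and contraceptives are a different matter. The table labels the item a self-efficacy measure, and the Zimbabwe setting section says the Sisters programme already offers these services.
- *Safe place (AGYW).* DREAMS uses safe spaces, so attending a DREAMS group can satisfy the item. The wording names no DREAMS venue, so other meetings can satisfy it too.

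By count, this touches one of ten AGYW mediators (in part) and three of eight Zimbabwe mediators (one in full, two in part).

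**Illustration (all inputs assumed).** Let *s* be the probability that an exposed girl attends DREAMS sessions (0 if unexposed). Let *b* be the probability that any girl meets peers elsewhere. The item is positive if either happens. The outcome depends on DREAMS attendance only, so true psycho-social mediation is zero.

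- Item positive if exposed: s + (1 − s)b. If unexposed: b.
- Difference: s(1 − b).
- Total effect on the outcome: δs, where δ is the effect of attending.
- Outcome difference by item status among the exposed: δs / [s + (1 − s)b].
- Apparent mediated share: s(1 − b) × δs / [s + (1 − s)b] ÷ δs = s(1 − b) / [s + (1 − s)b].

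For s = 0.6 and b = 0.2: exposed 0.6 + 0.4 × 0.2 = 0.68, unexposed 0.20, difference 0.48, share 0.48 / 0.68 = 0.706. A simulation of this case also gave 0.706.

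| s | b | Exposed | Unexposed | Difference (points) | Apparent share |
|---|---|---|---|---|---|
| 0.4 | 0 | 40% | 0% | 40 | 100% |
| 0.4 | 0.2 | 52% | 20% | 32 | 62% |
| 0.4 | 0.6 | 76% | 60% | 16 | 21% |
| 0.6 | 0 | 60% | 0% | 60 | 100% |
| 0.6 | 0.2 | 68% | 20% | 48 | 71% |
| 0.6 | 0.6 | 84% | 60% | 24 | 29% |
| 0.8 | 0 | 80% | 0% | 80 | 100% |
| 0.8 | 0.2 | 84% | 20% | 64 | 76% |
| 0.8 | 0.6 | 92% | 60% | 32 | 35% |

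If the planned 400 per age group split into 200 exposed and 200 unexposed (also assumed), step 1 has at least 93% power to detect the built-in difference for every combination run with b from 0.1 to 0.6.

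The either-or form suits the safe-place item. The mobilisation item requires attendance and cohesion together, so the table illustrates only its attendance part.

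**The case against.** The strongest reply is that the overlap is narrow and the list provisional. The block is headed as sample measures, in a condensed article. Social assets and personal safety are among the named constructs, and meeting peers in a safe place fits them. The access item is expressly a self-efficacy measure. The four causal steps are written for the nested AGYW cohorts; for Zimbabwe the article says only that the cohort can be used to study pathways, and design details unique to that site are published separately.

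Most of this stands, and it limits the point. It does not remove it: Table 3 is titled as what the cohorts will capture, for Zimbabwe as well, and nothing shown separates the overlapping items from uptake.

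A reader might go further and infer that these mediators simply are receipt of DREAMS, so that the pathway question is answered by definition. The documents do not support that:

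- Nine of the ten AGYW mediators, such as a trusted friend, ability to refuse sex, savings and shared-decision beliefs, are distinct from receipt.
- The mobilisation item includes a psycho-social state. The mobilisation component in Table 1 is aimed at leaders, boys and men, so the sessions are not shown to be exclusive to DREAMS.

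A reader might also infer that the arm fixes the mediator in Zimbabwe, with access near zero in the "four comparison sites in which no DREAMS interventions are planned". Women there are referred to Sisters, which provides every listed service in the access item except PrEP. PrEP is not among the Sisters services listed, so low PrEP access there is a fair inference, but no figure is given.

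**Conclusion.** The point holds at item level. It is clearest for the Zimbabwe mobilisation item and for PrEP support and access, and partial for the AGYW safe-place item. For these items, and any composite that includes them, step 1 is partly true by construction and a step 4 share blends receipt with mechanism. The remaining mediators can be interpreted as planned.

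The size depends on how often an item is met outside DREAMS. Over the assumed ranges (s from 0.4 to 0.8, b from 0 to 0.6), the built-in difference is 16 to 80 percentage points and the false mediated share 21% to 100%. The distortion is severe where only DREAMS can satisfy the item and milder where it is commonly met elsewhere. These figures rest on assumed inputs and on a model in which meeting peers elsewhere has no effect on the outcome. They are not estimates for any site.

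**What to change.** 1. Split the Zimbabwe mobilisation item. Keep social cohesion as a mediator and count session attendance as a measure of uptake or receipt.
2. Treat PrEP support and PrEP access as receipt measures, and separate them from the condom, STI treatment and contraceptive part of the access item, which stays as self-efficacy. Do not estimate mediated shares through the PrEP measures where PrEP receipt defines the exposure. Analyse them within the intervention sites.
3. Keep the safe-place item as a social-asset mediator, and report steps 1 and 4 with and without it. Moving it to the uptake block would be a mistake, because girls who meet peers safely outside DREAMS would be counted as exposed.
4. Apply the same separation to any composite mediator score.

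The cost is slightly fewer mediators and one extra sensitivity analysis. No new data collection is needed, provided that attendance and cohesion, and PrEP and the other services, are recorded as separate answers.
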